	The Michigan Hand Outcomes Questionnaire (MHQ) [24, 25]	assesses right and left hands separately: physical status of the hand (movement, strength, sensation: 5 items); daily activities performed with the hands/arms (5 right and left; 7 bilateral); impact of their condition on their normal activities (5 items); pain frequency, severity and impact (5 items); perceived appearance of their hands (4 items); satisfaction with hand abilities (6 items)	✓	✓
Disability	The Health Assessment Questionnaire [26]	24 items of daily function	✓	✓
Economic analysis	EQ5D-3 L [27, 28]	5-items Scale (Mobility; Self-care; Usual activities; Pain/Discomfort; Anxiety/Depression	✓	✓
	Your use of NHS and social services	a) Any planned hospital overnight stays in the last 3 months b) List of planned admissions	✓	✓
	Your use of hospital out-patient appointments	a) Any planned hospital outpatient appointments lasting 4 h or less in the last 3 months b) If yes, department, speciality and number of appointments	✓	✓
	Your use of day hospital appointments	a) Any day or hospital outpatient lasting more than 4 h but not overnight during the last 3 months b) If yes, department, speciality and number of appointments	✓	✓
	Your use of accident and emergency services	a) Any A&E attendance in the last 3 months b) If yes, the number of visits did not lead to hospital admission c) Were admitted into a hospital as an in-patient from the A&E d) If yes, department, reason for admission, where and when admitted	✓	✓
	Your use of primary and community based health services	a) Use of services such as GP, Practice nurse, Nurse, Counsellor in the last 3 months b) If yes, number of visits to each	✓	✓
	Your use of primary and community based health services	a) Use of services such as, occupational therapy, Physio, Care worker, Home help, Social worker, Other in the last 3 months b) If yes, number of visits to each	✓	✓
Medication	Current medication for RA/IA			✓
	Any steroid injection/oral steroids started in the last 12 weeks	Yes/No		✓
	If yes, the date of the injection/started taking oral steroids	DD/MM/YY		✓
Health Status	Your own health state today	Measured by a 0-100 vertical scale (0 = worst imaginable state & 100 = best imaginable health state)		✓
Additional outcomes	Any other upper limb occupational therapy or physiotherapy treatment received in the last 12 weeks	Type of treatment received		✓
	Whether purchased or obtained from elsewhere, any other “arthritis” gloves.	Yes/No		✓

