### Data collection methods

Outcomes will be collected via self-reported questionnaires at baseline (i.e. prior to randomisation) and 12 weeks later. Glove provision will usually occur within three weeks of randomisation and referral to occupational therapy. Thus, at follow-up, most participants will have worn gloves for about nine weeks. Feedback from glove users indicates that they normally experience any benefits within a short-time of commencing glove-wear.

The trial manager (baseline) and CTU (12 weeks) will monitor return of all questionnaires and the quality of data.
**At 1 week** after questionnaire provision/mailing, if the questionnaire is not yet returned, the trial manager [baseline questionnaire] or CTU [12-week questionnaire] will telephone/text/e-mail (as applicable) to remind the participant to return their questionnaire.
**At 2 weeks** after questionnaire provision/mailing, if the questionnaire is not yet returned, the trial manager [baseline questionnaire] or CTU [12-week questionnaire] will mail a reminder letter and a further copy of the relevant questionnaire (with Freepost envelope).
**If the 12 week questionnaire is not returned by week 16,** the CTU will inform the trial manager who will then telephone the participant to obtain a minimal data set (i.e. at least dominant hand pain during moderate activity and if gloves are being worn (yes/no)). If possible, as much of the following will also be collected: dominant hand pain at night; hand stiffness; MAPHAND; hand condition severity scale; how their hands are in comparison to 12 weeks ago, i.e. before receiving gloves (much better/better/no change/worse/much worse). The trial manager will complete the minimal dataset on a 12-week questionnaire (with participant’s PIN included), identifying on the front page that it is a minimal dataset completed by telephone. If the trial manager is unable to obtain this data, this will be recorded in the Trial Database and data entered as missing.

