#### Economic evaluation

The economic analysis will include costs to health and social care service providers and health benefits to patients. The time horizon for the evaluation is 12 weeks as per the scheduled trial follow-up. As such neither costs nor outcomes will be discounted. The data will be analysed on an intent-to-treat basis.

The measure of health benefit for the primary economic analysis will be quality adjusted life years (QALYs). This will be estimated from the EQ-5D-3 L and associated utility tariffs. Secondary analysis will explore the cost-effectiveness of arthritis gloves using the primary clinical outcome measure, change in hand pain during moderate activity between baseline and follow-up. The direct costs of healthcare resources used during the trial will be estimated by combining the level of use reported by participants with the unit cost specific to that resource. The unit costs will be derived from published national average unit cost data, the price year will be 2016. Total direct costs will also include the cost of the gloves. Regression analysis will be used to estimate the net total costs and economic benefits of the arthritis gloves compared to the placebo gloves, adjusting for baseline values and the stratification variable (recent DMARD changes).

Cost-effectiveness will be measured as an incremental cost-effectiveness ratio (ICER) for the arthritis gloves versus the placebo gloves. As recommended by NICE for health technology appraisals [34], cost-effectiveness acceptability analysis will be conducted. Non-parametric bootstrapping of the incremental costs and outcomes (estimated from the regression analysis) will be used to estimate the probability that arthritis gloves are cost-effective compared to placebo gloves.

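### The week-16 telephone data set lists neither the EQ-5D-3L nor steroid use, leaving avoidable gaps in the primary economic analysis and the steroid-exclusion sensitivity analysis

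*Protocol article*

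**What the plan says.** Data collection methods (Protocol article) sets out the last step for late responders. The trigger is "If the 12 week questionnaire is not returned by week 16". The trial manager then telephones for a minimal data set, "at least dominant hand pain during moderate activity and if gloves are being worn (yes/no"). An optional list follows: "If possible, as much of the following will also be collected: dominant hand pain at night; hand stiffness; MAPHAND; hand condition severity scale", and perceived change since before the gloves. On recording, the section says "The trial manager will complete the minimal dataset on a 12-week questionnaire", marked on the front page as a telephone minimal data set.

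Economic evaluation states "The measure of health benefit for the primary economic analysis will be quality adjusted life years (QALYs"), and of that measure, "This will be estimated from the EQ-5D-3 L and associated utility tariffs". No other source of utility is named. Costs come from resource use reported by participants. The section adds "The data will be analysed on an intent-to-treat basis". It does not say how missing utilities or costs are handled.

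Statistical methods plans a sensitivity analysis of the primary outcome that excludes, among others, participants who had steroids between randomisation and outcome measurement. The 12-week item in Table 1 that supplies this is "Any steroid injection/oral steroids started in the last 12 weeks", paired with a date. The same section rules out imputation for the primary clinical analysis.

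**The concern.** The article fixes which items are asked on the call, and that list does not match what the planned analyses need. It includes the 18-item MAPHAND, a secondary outcome, but not the 5-item EQ-5D-3L, on which the benefit side of the primary economic analysis rests. It also has no question on steroids, although steroid status defines a planned sensitivity set.

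How a missing value is analysed can be left to an analysis plan. Whether it is collected cannot, because a utility that was never asked for cannot be recovered later. At stake are the completeness and precision of the QALY comparison, and correct classification in the steroid-exclusion analysis. Both losses fall on late responders, whose pain scores are observed and used.

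**Working it through.** **1. Item lists side by side**

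| Needed for | Item | On the 12-week questionnaire (Table 1) | On the telephone list |
|---|---|---|---|
| Primary clinical analysis | Dominant hand pain in activity | Yes | Yes, required |
| Primary economic analysis, benefit | EQ-5D-3L (5 items) | Yes | No |
| Primary economic analysis, cost | Resource use (six blocks) | Yes | No |
| Steroid-exclusion sensitivity analysis | Steroid started, with date | Yes | No |
| Secondary outcome | MAPHAND (18 items) | Yes | Yes, optional |

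**2. Other sources of steroid status.** Under Recruitment, the therapist identifies steroids started between consent and glove fitting. The article describes no systematic record of steroids started after fitting other than the 12-week questionnaire.

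**3. The plan's own sample size**

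- Inputs (Sample size): difference 1.1, SD 2.48, alpha 0.05 taken as two-sided, power 80%.
- Per group: 2 × (1.960 + 0.842)² × 2.48² / 1.1² = 79.8, so 80. This agrees with the plan.
- Total: 160 / (0.80 × 0.98) = 204.1, or 160 / (1 − 0.22) = 205.1. Both are consistent with 205, so the stated figure stands and this point does not affect it.

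**4. How many could reach the call.** Sample size explains the 20% attrition mainly as non-return of the 12-week questionnaire. On that reading 0.20 × 205 = 41 could reach the telephone step, and 0.80 × 205 = 164 return a questionnaire containing the EQ-5D-3L.

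**5. Precision lost.** Let q be the share of all 205 who answer only by telephone. The article gives no figure, so q = 0.05, 0.10 and 0.15 are assumed. Suppose the standard error varies as 1/√n, with similar spread and an even split between arms. The ratio of the standard error without the EQ-5D-3L to that with it is then √[(0.80 + q) / 0.80].

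| q | People (205q) | Ratio | Increase in SE |
|---|---|---|---|
| 0.05 | about 10 | √1.0625 = 1.031 | 3% |
| 0.10 | about 21 | √1.125 = 1.061 | 6% |
| 0.15 | about 31 | √1.1875 = 1.090 | 9% |

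If the 20% were instead people lost even after the call, telephone responders would come out of the remaining 80%. The ratio would be √[0.80 / (0.80 − q)] = 1.033, 1.069 and 1.109, that is 3%, 7% and 11%. The first reading fits the article's wording better and is the one carried forward.

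**6. Bias.** This would depend on how far the arm difference in utility among telephone responders departs from that among postal responders. The article gives nothing from which to set that, so no figure is offered.

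**The case against.** **The list is a minimum.** Two items are required, others are optional, and answers go onto a full 12-week questionnaire, so further items are not forbidden. This stands. A reader might infer that every telephone responder lacks a utility; the article shows only that none is planned.

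**Exclusion is not established.** A reader might infer that these participants drop out of the primary economic analysis, and that it is therefore not intention-to-treat. Neither follows. Handling of missing economic data is not stated and may sit in an analysis plan. The no-imputation sentence is in the clinical Statistical methods section. Missing outcomes do not of themselves undo analysis by allocated group.

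**Adding the EQ-5D-3L does not complete the economic data.** Resource use is also absent from the call, so costs would still be missing. This stands, and limits what the change achieves.

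**Timing.** The call comes after week 16 while the economic horizon is 12 weeks, so the utility would be late and collected by a different mode. That is true, but the same lateness is already accepted for the pain score. Table 1's steroid wording, looking back 12 weeks from a call after week 16, would not reach randomisation and so could not be reused as it is.

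**A minimal data set is a trade-off.** It protects the primary outcome in reluctant responders, and ranking one optional measure above another is a matter of judgement. That is accepted: nothing here requires the EQ-5D-3L to come before MAPHAND. But call length does not explain leaving out five items from an optional list that already holds eighteen.

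**Conclusion.** The concern holds as a gap in the data collection plan, not as a numerical error or a contradiction. Under the listed items, a participant reached only by telephone has observed data for the primary clinical analysis, but no planned follow-up utility or cost and no listed questionnaire source for steroids started after fitting. In the economic and steroid-exclusion analyses that person must be excluded or imputed.

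The size is modest: up to 41 people could reach the call, and the standard error of the QALY difference would be about 3% to 9% larger for 5% to 15% answering only by telephone. Those shares are assumed. The percentages also suppose a complete-case comparison and that everyone telephoned would have answered the EQ-5D-3L; imputation, or partial response to the added items, would make the difference smaller. The article does not show that late responders differ from prompt ones, so bias is possible but unquantified. The steroid gap affects a sensitivity analysis only.

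**What to change.** In Data collection methods, add to the optional telephone list:

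- the five EQ-5D-3L items;
- one question on whether steroids, by injection or by mouth, were started since randomisation, with the date.

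Keep the front-page telephone flag and record the date of the call, so that late utilities collected by telephone can be examined separately.

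The cost is a slightly longer call, with no extra visits or staff. The added utilities will be measured after week 16 and by a different mode from the postal ones. Costs for these participants will remain missing unless the six resource-use blocks are also asked, which would lengthen the call considerably, or are imputed.

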### Data management

#### Data transfer from the University of Salford to CTU

The trial manager will ensure copies of all completed baseline and completed/corrected 12-week questionnaires are provided, in a timely and secure manner (e.g. copies of the questionnaires will be scanned and sent by e-mail using encrypted PDF), to the CTU for data entry. PDF scans of the questionnaires will be securely stored in password protected restricted access folders on the University of Central Lancashire network.

A written Data Management Plan (DMP), containing more detail about the Data Management procedures is available on request from the research team.

Baseline and 12 week questionnaires will be securely stored at the CTU following CTU procedures. At the end of the study, all electronic copies of participant questionnaires will be deleted and purged from the CTU network. Any paper questionnaires and documents (originals or copies) will be securely transferred to the University of Salford. Interview recordings will be deleted following transcription and analysis. Recordings and transcriptions will be stored on a secure server at the University of Salford. All data will be archived for three years in the Centre for Health Sciences Research, University of Salford. Quantitative data will become available to other researchers, on request, following completion and publication of the trial.

### Statistical methods

Primary effectiveness analyses will follow a pre-specified statistical analysis plan and will include the intention to treat (ITT) population. The primary analysis will use multiple linear regression to estimate the effect of group allocation on hand pain during activity, controlling for the stratification variable in the randomisation process (recent DMARD changes) and for the baseline value of the hand pain score. Secondary analysis will repeat the primary analysis method for all other outcomes, using appropriate modelling approaches (i.e. multiple linear regression, logistic regression or ordinal logistic regression, controlling for the stratification variable and the baseline value of the specific measure. Sensitivity analyses will assess for any potential bias in the analysis of the primary outcome measure by excluding participants who were not given gloves, were given the wrong gloves, or who received steroids (oral or injection) between randomisation and outcome measurement (per protocol populations). Data will be analysed by person and using dominant hand results, as reported by the participant. No interim outcome analysis or sub group analysis will be undertaken. We will not undertake any data imputation for the primary analysis. We will undertake multiple imputation of the primary outcome as a sensitivity analysis. Questionnaire responses on medication use, other treatments, perceived benefit of gloves, continued glove use, adherence and occupational therapist treatment record data will be reported as numbers/proportions or means/SD, with 95% confidence intervals. Analyses will be undertaken in Stata version 14 or later [33].

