### Sample size

This was calculated using data from the feasibility study. Minimal clinically important differences for pain scales in RA are estimated as 1.1 points on a 0–10 scale [31, 32]. The mean change in hand pain score during activity (measured four weeks post-intervention) was -1.03 (SD 2.22). As the SD from the feasibility data might be an underestimate, the 80% upper one-sided confidence limit of the estimated SD, i.e. 2.48 was used. To identify a 1.1 point difference, SD = 2.48, p = 0.05 and 80% power, 80 participants are required per group. Allowing for a 20% attrition (i.e. non-return of 12 week questionnaire and a small number (up to 2%) not receiving a glove for their dominant hand (because they only require a glove for their non-dominant hand, and therefore not providing primary outcome data), we intend to recruit 205 participants.

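### The exclusion analyses are offered as a check for bias but break the randomised comparison, and imputation resting mainly on baseline data would not test departures from missing at random

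*Protocol article*

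**What the plan says.** Statistical methods (Protocol article) sets the primary analysis as a linear regression of 12-week hand pain on allocated group, adjusted for baseline pain and the DMARD-change stratum, by intention to treat and without imputation. For missing data it adds one check: "We will undertake multiple imputation of the primary outcome as a sensitivity analysis". It also plans sensitivity analyses meant to look for bias in the primary result by "excluding participants who were not given gloves, were given the wrong gloves, or who received steroids (oral or injection) between randomisation and outcome measurement", and calls the resulting sets per-protocol populations. The imputation variables and the missingness assumption are not given. The section refers to a pre-specified SAP, which is not shown.

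Three other places bear on this:
- Data collection methods: outcomes are collected at baseline and 12 weeks only. If the questionnaire is still out at week 16, the trial manager telephones "to obtain a minimal data set (i.e. at least dominant hand pain during moderate activity" plus whether gloves are worn); other items follow where possible.
- Sample size: "Allowing for a 20% attrition", made up of questionnaire non-return and a small number without a dominant-hand glove.
- Recruitment: the protocol itself notes that steroids can lower hand pain and confound the evaluation of the gloves.

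**The concern.** A check for bias should hold when the primary analysis might fail. Neither check, as described, clearly does.

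The exclusions all rest on events after randomisation. Starting steroids plausibly follows from hand pain, which is the outcome. If the gloves work, steroid starters will differ between arms, and removing them leaves groups that are no longer comparable. Whether a glove is fitted depends partly on therapist judgement (Glove fitting), and therapists know the allocation (Blinding). The two arms also use different makes and fitting rules, so non-fitting could differ by arm; the documents give no size ranges by make, so this is only a possibility.

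The primary regression is valid if outcomes are missing at random given arm, baseline pain and stratum. With one follow-up, a participant who returns no questionnaire and is not reached by telephone has little post-baseline data. Imputation that makes the same assumption from much the same variables should then give much the same answer. Non-response need not be balanced: the Harms section attributes most adverse events to pressure, so discomfort-driven loss could fall mainly in the intervention arm.

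At stake is how agreement between analyses is read. It could be reported as robustness when the relevant departure was not examined.

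**Working it through.** **1. The plan's own figure.** Inputs from Sample size: "To identify a 1.1 point difference, SD = 2.48, p = 0.05 and 80% power, 80 participants are required per group".
- n per group = 2 × (1.960 + 0.842)² × 2.48² / 1.1² = 79.8, so 80, taking p = 0.05 as two-sided. This reproduces the plan.
- SD limit: 2.22 × √(38 / χ² at 0.20 on 38 df) = 2.476 for n = 39, against the stated 2.48.
- Inflation: 160 / 0.78 = 205.1, or 160 / (0.80 × 0.98) = 204.1; the plan has 205.
- Planned standard error = 2.48 × √(2/80) = 0.392.

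**2. Excluding steroid starters.** All parameters are assumed; the true effect is −1.10.
- Trials of 160, 1:1, baseline SD 2.2, steroid start logistic in latent pain, no effect of steroids on the outcome:

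| Slope per point of pain | Steroid use, intervention / placebo | All participants | Starters excluded | Bias against −1.10 |
|---|---|---|---|---|
| 0.3 | 13% / 18% | −1.11 | −1.08 | 0.02 |
| 0.8 | 12% / 22% | −1.10 | −0.96 | 0.14 |

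- A second set (N = 1,000,000, SD 2.2, correlation 0.5, slopes 0.2 to 0.4, steroid effect 1 to 2 points, 10 to 30% steroid use) gave a bias of 0.01 to 0.10.
- In these runs the exclusion pulled the estimate towards the null.

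**3. Complete-case regression against imputation.** Trials of 205, 20 imputations, 1,500 repeats, true effect −1.10. All parameters are assumed.

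| Missingness depends on | Share missing | Complete case | Imputation, primary-model covariates | Imputation plus a post-baseline variable that drives missingness |
|---|---|---|---|---|
| Baseline pain | 20.5% | −1.09 | −1.09 | −1.09 |
| Post-baseline experience, intervention arm, weaker | 16.3% | −1.23 | −1.22 | −1.10 |
| Post-baseline experience, intervention arm, stronger | 19.4% | −1.37 | −1.37 | −1.09 |

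With the primary model's covariates only, imputed and complete-case estimates correlated at 0.995 or more and shared the same bias, up to 1.37 − 1.10 = 0.27 points in favour of the gloves. A suitable post-baseline variable removed it.

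**4. Tipping point.** If a share m of the intervention arm is missing and truly worse than imputed by δ, the difference shrinks by m × δ. Significance is lost at δ = (observed − 1.96 × 0.392) / m, where 1.96 × 0.392 = 0.769 and the change in variance is ignored. For an observed 1.1:

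| m | δ (points) |
|---|---|
| 10% | 3.31 |
| 15% | 2.21 |
| 20% | 1.66 |
| 22% | 1.51 |
| 30% | 1.10 |

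With a t multiplier of 1.975 the 20% figure is (1.1 − 0.774) / 0.2 = 1.63. For an observed 0.90 it is (0.90 − 0.774) / 0.2 = 0.63. Shares other than 20 to 22% are assumptions.

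**The case against.** A reader might infer that the planned checks cannot test the primary result at all, or that the imputation uses baseline data only. The documents do not support either reading. The protocol does not state the imputation model, and variables, assumptions and any shift analysis are commonly left to the SAP, so their absence here is no finding. Post-baseline information may also exist. Treatment records hold glove problems and adverse events, although some departments review only on request. A returned questionnaire with a blank pain item would carry other 12-week scores. Participants with a non-dominant-hand glove only could still report secondary outcomes. Step 3 shows that such data can matter.

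The size can also be overstated. The 20% allowance is largely questionnaire non-return, and the telephone call seeks exactly the primary score. If it recovers half (an assumption), the tipping shift for 1.1 is about 3.3 points. The SE of 0.392 is unadjusted and uses an SD set at its upper limit; with the adjusted 0.344 from the first scenario in step 3, the 20% figure becomes (1.1 − 1.96 × 0.344) / 0.2 = 2.13. An observed 0.90 lies close to the threshold of about 0.77, so its fragility is partly built in.

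The exclusions are openly called per-protocol and are secondary to an intention-to-treat analysis that keeps these participants. Their simulated bias is modest and towards the null, so it would not manufacture a benefit. Non-fitting is largely anatomical under Modifications.

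All of this stands as a limit on the size of the point. It does not rescue the purpose the protocol gives the exclusions: an analysis that can introduce bias cannot show whether bias is present.

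**Conclusion.** The point holds in a limited form. The exclusion sets are defined by post-randomisation events and should not be presented as a check for bias. In simulation, dropping steroid starters moved a true 1.1-point effect by about 0.01 to 0.14 points towards the null; this range depends wholly on assumed links between pain and steroid use. The effect of excluding unfitted or wrongly gloved participants was not simulated.

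On missing data the conclusion is conditional. If imputation assumes missing at random and draws mainly on baseline variables, it will nearly reproduce the primary estimate and leave departures from that assumption untested. For an observed 1.1 at SE 0.392, the intervention-arm shift that removes significance is about 1.6 points at 20% missing and about 3.3 at 10%. For scale, the protocol takes 1.1 points as the minimal clinically important difference. The true missing share is unknown.

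Neither part undermines the primary intention-to-treat analysis or the sample size. What changes is what the supporting analyses may be said to show.

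**What to change.** 1. Label the exclusion analyses as supplementary per-protocol descriptions and remove the statement that they assess bias. Keep steroid starters' observed scores in the intention-to-treat analysis. Setting those scores to missing and imputing them is no improvement: in simulations with assumed parameters it agreed with simple exclusion to within 0.004 points.
2. For participants with no gloves or the wrong gloves, add a complier-average estimate with randomisation as the instrument, keeping everyone randomised. The cost is a wider interval and an exclusion restriction that must be stated: allocation affects pain only through the glove received.
3. Make the imputation analysis delta-adjusted. Shift imputed scores over a range, for example 0 to 2.5 points and wider if the tipping point is not reached, in the intervention arm only, the placebo arm only and both. Report the shift at which the confidence interval first includes 0, beside the observed missing share in each arm.
4. Put treatment-record data and any partial 12-week responses in the imputation model. If the SAP already covers items 3 and 4, only a cross-reference is needed.

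The cost is SAP wording and a few extra Stata runs, with no new data.
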